#### Exit criteria

The following criteria will mandate the discontinuation of the intervention in both arms and a return to standard of care, as these are considered side effects of the medication if they occur within 1 to 3 days of administration of the medication: profound hypotension requiring > 30 mL/kg fluid bolus and inotropic support of ≥20 mcg/kg/min of intravenous dopamine or dobutamine, thrombocytopenia of ≤100,000/mm3, and arrhythmia requiring treatment.

#### Randomisation and allocation

A computer-generated central randomisation scheme will be used to assign the infants to the two arms in a 1:1 ratio. Each infant will be assigned a unique 3 digit identification (ID) number. The study pharmacist in each centre will receive a binder containing the sequence of treatment group assignments for the cohort from a statistician who will not otherwise be involved in the study. At each study center, access to the binder will be restricted to selected pharmacy personnel, and will be kept locked in a secure locker in the pharmacy department.

#### Concealment and blinding

Both formulations are clear and colourless. The ampoules used will be identical and will have a study identification number included in the label on the ampoule. This number will be known to the study pharmacist. Once a patient is recruited and randomised to either Milrinone or Placebo, the trial pharmacist or physician not involved in recruitment, allocation, and data collection will prepare the trial drug or placebo and issue the syringe for infusion to the trial investigator team for administration. An on call arrangement will be devised for out of hours preparation. The milrinone preparation is colourless and odorless and will be indistinguishable from the saline preparation used for the placebo arm. The designated pharmacist in each study centre will be aware of the treatment allocation in order to facilitate correct assignment and drug/placebo preparation. The trial participants and their families, the care providers, the data collectors, the echocardiographers, the primary outcome assessors, and the data analysts will all be blinded to the allocation.

#### Monitoring, outcome measures and participant timeline

The primary outcome of this study is the time on iNO in hours and the time on invasive ventilation. A standardised protocol for iNO weaning is detailed in Additional file 2.

We will collect the following demographic characteristics and relevant short-term secondary outcomes: duration of hospital stay; time to extubation; duration of oxygen therapy, and survival.

**Details of cardiorespiratory stability** (blood pressure, heart rate, oxygen saturation), ventilation support (FiO_2_, mean airway pressure (MAP), oxygenation index [MAP × F FiO_2_/PaO_2_]), efficacy of oxygenation [PaO_2_], plasma lactate, pH, PCO_2_, HCO_3_^−^, Base excess; and relevant co-treatments (i.e., sedation, analgesics, muscle relaxants, inotropes, fluid administration) at the following time points:Prior to treatmentFollowing the loading dose12 h after initiation of therapy24 h after initiation of therapyTwo hours after discontinuation of therapy

**Monitoring of blood parameters** will be carried out as follows during the study period and 24 h after drug discontinuation:Full blood count (including platelets): dailyElectrolytes, Urea and Creatinine: dailyLiver function tests (ALT, AST, GGT): dailyBlood gas analysis: 12 hourly

**Echocardiography** will be performed according to the following schedule: a timing window of ±3 h will be applied. Scans performed outside the ±3 h window will constitute a protocol deviation:Prior to the Commencement of Study Drug: Diagnose PPHN and rule out CHD12 h following the administration of Study Drug24 h following the administration of the study drug8 h following the discontinuation of the study drug

**Non-invasive Cardiac output Monitoring (NICOM)** will be commenced prior to the commencement of the study drug and continued until the last echocardiogram, 8 h after the discontinuation of the study medication.

**Cranial ultrasound** will performed prior to treatment commencement and after the discontinuation of the infusion. Intraventricular haemorrhage will be defined and graded with the Papile classification [30]. Echocardiography will be carried out at baseline as detailed above and at 12 h, 24 h, 2 h after discontinuation of therapy, and before discharge.

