## Introduction

### Scope of the problem

Persistent pulmonary hypertension of the newborn (PPHN) is a relatively common condition occurring in 0.5 to 7 per 1000 live births and results in a mortality ranging between 4 to 33% [1, 2]. Inhaled nitric oxide (iNO) and extracorporeal membrane oxygenation (ECMO) are the only current therapeutic options that are systematically evaluated in clinical trials [3, 4]. The vasodilatation induced by iNO is mediated by increasing concentrations of the second messengers: cyclic guanyl monophosphate (cGMP) and cyclic adenosine monophosphate (cAMP) in pulmonary vascular smooth muscle. The widespread use of iNO has resulted in a reduction in the need for ECMO; however, mortality and long-term morbidity remain unchanged [1, 4]. In addition, up to 40% of infants treated with iNO either have a transient response or fail to demonstrate an improvement in oxygenation [4, 5]. iNO does not improve myocardial performance in infants with PPHN, which often accompanies the condition and may contribute to mortality. Furthermore, the increasing cost of administering iNO to infants with PPHN may prohibit its use in developing countries. Due to these challenges, there is a real need to evaluate novel approaches to the management of PPHN.

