### Rationale for milrinone use

PPHN is common and leads to a major burden of neonatal illness, carries a significant mortality, need for ECMO, and adverse neurodevelopmental outcome. There is poor appreciation of the physiologic determinants of PPHN and predictors of iNO response at presentation; up to 40% of infants do not respond to iNO treatment. The increasing cost of iNO may preclude its use in both the developed and developing countries. The use of milrinone in infants with PPHN as an adjunct to iNO is worth further exploration with preliminary evidence suggesting an improvement in both oxygenation and myocardial performance in this group of infants. It’s inotropic, lusitropic and pulmonary vasodilator properties make it an ideal agent to use in this setting and may improve response to therapy and reduce mortality associated with the disease.

A recent Cochrane review illustrated the lack of randomised controlled trials (RCTs) comparing the use of milrinone versus placebo or as an adjunct to iNO compared with iNO alone in the setting of PPHN and recommended limiting the use of milrinone in PPHN to the research setting [29]. It is important to systematically investigate the efficacy of milrinone in the setting of PPHN prior to widespread dissemination of this treatment.

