#### Intervention

Infants in the intervention arm will receive an intravenous loading dose of milrinone lactate injection (10 mg/10 mL) at a dose of 50 μg/kg administered over 60 min followed by a maintenance infusion, beginning at 0.375 μg/kg/min to a maximum 0.750 μg/kg/min. The duration of therapy is until discontinuation of iNO or a maximum of 35 h in adherence with the summary of product characteristics (SmPC) recommendation. A 10 mL/kg bolus of normal saline will be administered with the milrinone bolus over the same 1 h period.

A loading dose was chosen to ensure the rapid attainment of therapeutic blood concentrations. The slow rate of administration was chosen to minimize the risk of infusion-related adverse effects, such as hypotension. This dosing regimen was established following the recent pharmacokinetic study performed by our group and described above [27]. Dose increase will be performed in response to the need for oxygen (FiO_2_) to maintain adequate pre-ductal saturations (95% or greater). Dose incrementation will be carried out every 2 h following the bolus if the fall in FiO_2_ needed to maintain an adequate saturation is less than 20%. Dose escalation will be carried out as described below (Section “Product and placebo preparation and infusion regimen”). For example, if 2 h after administration, the FiO_2_ of an infant falls from 60 to 45% (< 20%) to maintain a saturation of 95% or greater, the rate of infusion will be increased based on the table below. This escalation will continue every 2 h until a reduction of FiO_2_ of 20% or greater is achieved down to 40% FiO_2_. The maximum dose will be 0.750 μg/ kg/min.

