#### Statistical methods

The HRB IP CTN clinical trial statistician will conduct all the statistical analyses. The primary outcome and most of the secondary outcomes are continuous variables. Continuous variables will be tested for normality by comparing the mean and median, a histogram representation of data, and the Shapiro-Wilk test for normality and will be presented as means (standard deviation) or median [inter-quartile range] as appropriate. Dichotomous variables will be presented as proportions and summarised in contingency tables. The *primary analysis of the primary outcome* will be performed using an independent t-test (or a Wilcoxon Rank Sum test as appropriate) to compare the difference in time on iNO and invasive ventilation between the two groups. A chi squared test (or Fisher’s exact test) will be used for the *primary analysis of the dichotomous secondary* outcomes. For the continuous secondary outcomes, a t-test will be used to compare normally distributed data, and Wilcoxon Rank Sum test will be used for skewed data. We will accept a *p* value of < 0.05 as significant. We will use SPSS (version 22) to perform the statistical analysis.

All enrolled infants will be analysed on an intention-to-treat basis, including infants that have not continued treatment for any reason. Analysis for the feasibility study will only be conducted once the recruitment of all patients is completed. No interim analysis of treatment effect will be conducted. We anticipate that recruitment will take 4 years to complete with an additional 6 months required for the measurement of the echocardiography data and statistical analysis.

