## Conclusion

### Significant savings for the health service

A positive outcome in this pilot study will pave the way for a definitive trial of the use of milrinone for the treatment of PPHN. Improving the response rate to iNO and reducing the time on iNO and mechanical ventilation will have substantial short and long-term benefits for the healthcare service. Reduced length of stay will significantly reduce hospital costs in the neonatal intensive care unit. In addition, iNO administration is expensive (up to €50 per hour). Milrinone is relatively cheap costing about €30 per patient. There is potential for substantial savings if the use of milrinone is successful in reducing time on iNO. The increasing cost of iNO may soon preclude its use in both developed and developing countries so this study is urgently needed.

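### Time on iNO counts an unsuccessful stop the same way as a successful wean, so a better iNO response on milrinone could lengthen this primary outcome

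*Protocol article*

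**What the plan says.** The section *Monitoring, outcome measures and participant timeline* defines the endpoint: "The primary outcome of this study is the time on iNO in hours and the time on invasive ventilation". On how iNO ends it adds only this: "A standardised protocol for iNO weaning is detailed in Additional file 2". Survival is listed there as a separate secondary outcome. Neither iNO response nor the reason for stopping iNO is listed.

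*Statistical methods* plans a t-test, or a Wilcoxon rank sum test where appropriate, "to compare the difference in time on iNO and invasive ventilation between the two groups". All enrolled infants are analysed by intention to treat, including those who did not continue treatment. *Primary objective* hypothesises a reduction, so fewer hours are better.

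On failure of iNO, *Scope of the problem* says that "up to 40% of infants treated with iNO either have a transient response or fail to demonstrate an improvement in oxygenation", and *Rationale for milrinone use* says that "up to 40% of infants do not respond to iNO treatment". On death, *Scope of the problem* says that PPHN "results in a mortality ranging between 4 to 33" per cent. The section on health service savings names two benefits together: "Improving the response rate to iNO and reducing the time on iNO and mechanical ventilation". *The relevance of the primary outcome* says that the pilot is to supply preliminary data and a standard deviation for the definitive trial's sample size.

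**The concern.** An iNO course can end because the infant was weaned, or because iNO did not work and was withdrawn, the infant went to ECMO, or the infant died. These are opposite results, yet the endpoint records each as a number of hours and treats a small number as good. Study drug also ends with iNO whatever the reason: "The duration of therapy is until discontinuation of iNO or a maximum of 35 h".

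The article expects milrinone both to raise the iNO response rate and to shorten time on iNO. If unsuccessful stops come early, the two benefits pull the endpoint in opposite directions. An infant whom milrinone turns from a failure into a responder moves from a short time to a full weaning time, and the milrinone arm looks worse for it.

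Two products of the pilot are at stake: the reported direction of effect on one of its two primary measures, and the standard deviation handed to the definitive trial, which would mix weaning times with failure times.

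**Working it through.** **No stated figure to reproduce.** The article gives 10 infants per arm (10 + 10 = 20) as a feasibility number. It gives no effect size, standard deviation, power or typical iNO duration. All hour values below are therefore assumptions.

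**Inputs.** *f* is the share of infants whose iNO ends unsuccessfully. The article's 40% is taken as an upper bound for placebo, and halving on milrinone is assumed. *R* is mean hours on iNO in weaned infants and *F* is mean hours in failures, both assumed. Milrinone is first taken to change *f* only.

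**Formula.** Arm mean = (1 − f)R + fF. Milrinone minus placebo = (f₀ − f₁)(R − F), with f₀ for placebo and f₁ for milrinone. With f₀ above f₁, the sign depends only on whether failures spend less time on iNO than weaned infants.

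**Base illustration: R = 72 h, F = 12 h, f from 40% to 20%.**
- Placebo: 0.6 × 72 + 0.4 × 12 = 48 h
- Milrinone: 0.8 × 72 + 0.2 × 12 = 60 h
- Difference: +12 h, so the arm with half the failures looks worse.
- To break even, weaning time on milrinone must fall to (48 − 0.2 × 12)/0.8 = 57 h, a cut of 21%.

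**Range.** With R = 72 h throughout:

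| Failure, placebo to milrinone | F (h) | Milrinone minus placebo (h) |
|---|---|---|
| 40% to 20% | 6 | +13.2 |
| 40% to 20% | 24 | +9.6 |
| 40% to 20% | 48 | +4.8 |
| 40% to 20% | 96 | −4.8 |
| 40% to 20% | 120 | −9.6 |
| 20% to 10% | 12 | +6.0 |

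**If only some non-responders are stopped early.** Let a share *s* of non-responders stop at 12 h and the rest stay on for 1.5 × 72 = 108 h. Then F = 12s + 108(1 − s). This equals 72 h at s = (108 − 72)/(108 − 12) = 37.5%. With non-response from 40% to 20%, the difference is +2.4 h at s = 50%, −2.4 h at s = 25% and −7.2 h at s = 0.

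**At the pilot's size.** This was simulated with 20,000 trials of 10 per arm, lognormal times with a coefficient of variation of 0.5, and a two-sided Wilcoxon test at 0.05.
- Base illustration, raw hours: the milrinone mean is longer in 74% of trials. Significant apparent harm occurs in 10.0% and significant benefit in 0.4%.
- Same infants, failures scored at an assumed 336 h so that they rank worst: the mean favours milrinone in 83% of trials. Significant benefit occurs in 10.6% and significant harm in 0.3%.

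**Standard deviation.** Under the same assumptions, weaned infants have SD 0.5 × 72 = 36 h and failures 0.5 × 12 = 6 h. The placebo mixture variance is 0.6 × 36² + 0.4 × 6² + 0.6 × 0.4 × (72 − 12)² = 777.6 + 14.4 + 864 = 1656, so the SD is 40.7 h around a mean of 48 h. For a fixed difference in hours, sample size scales with the variance: 1656/1296 = 1.28, or 28% more infants than weaning times alone would imply.

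**The case against.** The strongest objection is that the article does not show that surviving non-responders come off iNO early. Its 40% includes transient responders and describes oxygenation, not stopping. In the group's earlier pharmacokinetic study of 11 infants, oxygen requirement and oxygenation index did not improve on iNO. Yet iNO went on, milrinone was added a median of 7 h later, and the iNO dose then fell. Other pulmonary vasodilators are barred during the study, which may also keep infants on iNO. Infants are assessed once established on iNO and parents have 6 h to consider, so some very early failures may never be randomised.

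Most of this stands. A reader might infer that up to 40% of infants will score a short, favourable time and that a drug which rescues iNO response would therefore look harmful. The article does not support that: non-response is not a stopping rate, and the sign reverses if failures stay on iNO longer than weaned infants. The earlier study does not settle the matter the other way, because all its infants received milrinone and it cannot show how long placebo non-responders remain on iNO. ECMO and death are more plausible routes to an iNO course ended by failure, and the endpoint has no stated rule for them either.

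It can also be said that ventilation time, the other half of the primary outcome, would be long in surviving non-responders. That is a partial counterweight, but it does not correct the iNO result, and death or ECMO transfer can shorten ventilation time too.

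Additional file 2 and any analysis plan are not at hand and could hold a scoring rule, although the article describes the file as covering weaning. Finally, raw hours are a valid measure of cost, one of the article's reasons for the endpoint. That is a reason to keep them beside the clinical outcome.

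**Conclusion.** The concern holds in a conditional form. As the article defines and analyses it, time on iNO treats an unsuccessful end of iNO like a successful one. Where unsuccessful stops come earlier than weaning, a higher response rate on milrinone could mask or reverse a benefit, and the SD passed on would mix two kinds of time.

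The size is not known. In the illustrations it runs from about 13 h in the wrong direction to about 10 h in the right one, depending on how many infants stop for failure and when. In the mixed case the sign changes at 37.5% of non-responders stopped early. With 20 infants a statistically significant false harm is uncommon: 10% in the base illustration, and 31% if failure fell from 40% to zero. The main damage is therefore to the direction and SD carried into the definitive trial. The definition should be changed, because the ambiguity sits in a primary outcome and is cheap to remove.

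**What to change.** 1. Record on the data collection sheet why each iNO course ended: successful weaning, lack of effect, ECMO or death. The reason should be assigned blind to allocation.
2. Define the outcome as time to successful iNO weaning. Rank infants whose iNO ended for lack of effect, ECMO or death worse than all weaned infants, and compare arms with the Wilcoxon rank sum test that *Statistical methods* already names. Infants who respond poorly but are eventually weaned keep their actual time, so the rule also works if non-responders stay on iNO longer.
3. Report beside it the proportion successfully weaned in each arm, the mean and SD of weaning time among weaned infants for the definitive trial's sample size, and raw hours on iNO as a cost measure.

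The cost is one data field and a sentence or two in the outcome and analysis sections, with no extra infants or procedures. The small downside is that the main comparison becomes rank-based and does not itself give a difference or SD in hours; item 3 supplies the SD. Treating failure, ECMO and death as events competing with weaning would be an acceptable alternative.

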Milrinone administration was associated with an increase in LVO (*p* = 0.04), RVO (*p* = 0.004), RV strain (*p* = 0.01) and strain rate (*p* = 0.002), and LV s` (*p* < 0.001) and a` (*p* = 0.02) tissue Doppler velocity waves. There was a significant reduction in iNO dose, oxygen requirement over the subsequent 72 h (all *p* < 0.05). In addition, the administration of milrinone was associated with a reduction in mean blood pressure (*p* = 0.04) peaking at 6 h post administration. This was associated with a significant increase in the use of vasoactive inotropes at 6 and 24 h. However, blood pressure began to increase after 12 h of milrinone administration with a peak at 72 h (systolic BP *p* = 0.02, mean BP *p* = 0.03, diastolic BP *p* = 0.02) in spite of a reduction in the use of vasoactive inotropes over the same time period.

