#### Secondary objective

The aim is to compare: the incidence of the use of other inotropes; critically low LV and RV function and output measured by echocardiography and a non-invasive cardiac output monitor (NICOM); the rate of adverse effects associated with milrinone including the incidence of hypotension; and the pre-discharge outcomes in the two groups. In this pilot study, we aim to assess the practicality of instituting the protocol and contributing to a sample size calculation for a definitive multicentre study.

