Continuous LVO measurement using bioreactance is facilitated by the NICOM system. The measurement will take place during the entire study period. Bioreactance is the analysis of the variation in the frequency spectra of a delivered oscillating current when it traverses the thoracic cavity. This is obtained by placing four emitting and receiving electrodes in a manner that “boxes” the heart. Each electrode sensor strip consists of two contact points. Upper thoracic electrode strips will be placed over the mid-clavicles and upper back bilaterally. The lower electrode sensors are placed between the 6th and 7th intercostal spaces at the mid-axillary line. The electrode set will be replaced after 48 h of measurement to ensure adequate signal acquisition. NICOM measurement of SV and LVO will be blinded to the echocardiography and the clinical team by covering the screen displaying the values. The echocardiographic measurement of SV and LVO will be paired with the corresponding NICOM readings following study completion. The NICOM system stores each reading of SV and LVO. SVR will be measured by the NICOM system on an hourly basis as the mean blood pressure is entered into the machine.

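### The stated schedule for blood pressure, inotropes and fluids has no record between the end of the loading dose and 12 h, although the article reports the largest pressure fall at 6 h; transient episodes can be missed if incidence is taken from these time points

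*Protocol article*

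**What the plan says.** The Secondary objective section of the protocol article lists the incidence of use of other inotropes and "the rate of adverse effects associated with milrinone including the incidence of hypotension". Hypotension is the only adverse effect it names.

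The Monitoring, outcome measures and participant timeline section lists blood pressure among the cardiorespiratory details to be collected, together with "relevant co-treatments (i.e., sedation, analgesics, muscle relaxants, inotropes, fluid administration) at the following time points". Five points follow, run together in the text: "Prior to treatmentFollowing the loading dose12 h after initiation of therapy24 h after initiation of therapyTwo hours after discontinuation of therapy".

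The Introduction, in the results just before Rationale for milrinone use, reports that mean blood pressure fell after milrinone, "peaking at 6 h post administration". It continues: "This was associated with a significant increase in the use of vasoactive inotropes at 6 and 24 h". Pressure then began to rise after 12 h.

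The Intervention section gives the load over 60 min and then titrates on oxygen requirement: "Dose incrementation will be carried out every 2 h following the bolus", up to a stated maximum and for at most 35 h.

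The section on non-invasive cardiac output monitoring (NICOM) adds: "SVR will be measured by the NICOM system on an hourly basis as the mean blood pressure is entered into the machine". The monitor runs from before the study drug until 8 h after it stops.

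**The concern.** The two items that make up the haemodynamic safety comparison, hypotension and inotrope use, have a stated collection schedule that passes over the time at which the article reports the greatest effect on pressure. It also passes over the period in which the dose is being raised.

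Consider an infant who becomes hypotensive a few hours into the infusion, responds to saline and an inotrope, and is off the inotrope before 12 h. On these time points that infant looks the same as one who was never hypotensive. If milrinone causes such episodes, they will be more frequent in the milrinone arm, and losing them shrinks the observed difference. The pilot is meant to inform a definitive trial, so a falsely reassuring comparison would be carried forward.

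**Working it through.** The article gives no figure to reproduce here. The check is a timeline, with time zero at the start of the load.

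**1. The gap.** The load ends at 1 h (Intervention) and the next record is at 12 h (Monitoring). Gap = 12 − 1 = 11 h, which is 11/12 = 92% of the first 12 h and 11/35 = 31% of the maximum infusion time. The reported 6 h low point lies inside it. Of the two reported inotrope increases, the one at 6 h lies inside the gap and the one at 24 h coincides with a scheduled record.

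**2. Dose increases.** The rate table under Product and placebo preparation and infusion regimen has six rows, 0.375 to 0.750 μg/kg/min, hence five steps. Assume one row per step, taken consecutively. The steps then fall 2, 4, 6, 8 and 10 h after the bolus, i.e. at 3, 5, 7, 9 and 11 h, all inside the gap. The article does not state one row per step, and each step depends on the oxygen response, so in some infants steps could fall after 12 h.

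**3. Whether another stated source fills the gap.**

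| Source | What it covers | What it leaves out |
|---|---|---|
| Hourly NICOM entry | Mean pressure, entered to obtain vascular resistance; only stroke volume and left ventricular output are named as stored | Systolic and diastolic pressure, inotropes, fluids |
| Withdrawal rule (Use of additional inotropic and concomitant therapy) | Infants who fail to respond to treatment | Infants who respond |
| Exit criteria | Profound hypotension (more than 30 mL/kg fluid and at least 20 mcg/kg/min dopamine or dobutamine) | Lesser episodes |
| Data Monitoring Committee | Review of emerging adverse effects | No collection schedule of its own is stated |

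The section on additional inotropic therapy defines hypotension by the 3rd centile of systolic or of diastolic pressure. An hourly mean pressure cannot be classified against either.

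**4. Illustration of capture.** The article gives no episode duration or rate, so these figures only show how the schedule behaves. Assume one unbroken episode of D hours with onset uniform over 1–12 h, and count it as captured if it is in progress at a scheduled record.
- 12 h record alone: D/11. For D = 2, 4, 6 h: 2/11 = 18%, 4/11 = 36%, 6/11 = 55%.
- With a 6 h record added: [min(D, 5) + D]/11. For the same D: 4/11 = 36%, 8/11 = 73%, 11/11 = 100%.

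If 40% of an arm of 10 had one 4 h episode in this window, the expected recorded number would be 10 × 0.40 × 0.36 = 1.44 instead of 4. With the same capture fraction in both arms, the observed risk difference is that fraction times the true one, so the comparison moves towards zero.

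**The case against.** The strongest reply is that the five points are serial physiological readings and that the article never says incidence is counted from them. Hypotension and inotrope use are worded as incidences, hypotension triggers treatment whenever it occurs, a committee watches adverse effects, and the recording of events is detail that an article may leave to the full protocol. This stands against any claim that hypotension will be under-counted. A reader might infer that; the documents support only that it can be, if these points are the source.

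A reader might also infer that no blood pressure is taken until 12 h. That is too broad, because mean pressure is entered hourly.

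Nor is the schedule blind to harm. Pressure began to rise only after 12 h, so the 12 h record may still find it low, and the 24 h record coincides with the second reported inotrope increase. The pharmacokinetic study, which used the same load, found a transient systolic fall after the bolus, and the post-load record is placed to see it. All of this stands. What remains unseen is the reported peak and any episode over before 12 h.

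The text at hand does not show the dosing behind the 6 h finding. If it comes from the 17-infant observational study, milrinone ran for a median of 88 h there, against at most 35 h here. The timing may therefore not carry over exactly. It is still the article's own evidence on when pressure is lowest.

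Finally, a reader might argue that the last record, 2 h after stopping, comes too soon because the mean half-life is 4.1 h and 0.5^(2/4.1) = 71% of the drug remains. This adds little: that reading still reflects exposure, and NICOM continues to 8 h.

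**Conclusion.** The point holds in a conditional form. The stated schedule for systolic and diastolic pressure, inotropes and fluids has an 11 h gap that contains the reported 6 h low point and, with consecutive one-row steps, every dose increase. No other stated source supplies those data for infants who respond to treatment. If incidence is taken from the five time points, treated transient episodes can be missed and the safety comparison may be biased towards no difference.

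The size cannot be given from the article. The capture percentages above rest on an assumed duration and a uniform onset. The matter concerns secondary safety outcomes in a 20-infant pilot, not the primary outcome.

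**What to change.** In the Monitoring section, add a collection point at about 6 h, and record systolic and diastolic pressure, inotropes and fluids at the 2-hourly oxygen checks that the Intervention section already requires.

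State that, in both arms, incidence of hypotension and of inotrope use is derived from all episodes and starts during the infusion (lowest systolic and diastolic pressure, any inotrope or fluid start), not from the five time points alone. The data sheet should ask for these items directly, because the article does not say that hourly systolic and diastolic charts will be available.

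The cost is a few more data-sheet entries per infant in a trial of 20. No dose or treatment rule changes.
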